### Setting

Treatment-seeking participants with TUD according to the fifth version of the Diagnostic and Statistical Manual of Mental Disorders (DSM-5; [48]) will be randomised into four intervention arms. Assessments will take place before (baseline, T1) and after (second investigation day; T2) the six-week smoking cessation program, with a follow-up assessment (T3) three months later. A sport medical examination will be conducted at baseline at an outpatient cardiology clinic, while the other assessments will be conducted at the Central Institute of Mental Health, Mannheim, Germany.

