A total of 128 participants will be randomized into four groups (4 × 32 smokers), receiving add-on interventions alongside a smoking cessation program (SCP) [50]. The randomization protocol will control for sex. Stratified (men/women) block randomization with permuted blocks of size 8 will be used. Groups 1 and 2 will receive CRT + HIIT either in the evening or morning, respectively. Group 3 and Group 4 will receive only HIIT in the evening or morning, respectively. Each subject will undergo three days of investigation. Assessments will occur before SCP (baseline, T1), after a six-week SCP (T2), and at a follow-up appointment three months later (T3). An in-house smartphone application will be used to remind participants about the exercises and to collect accompanying information, i.e., physical exertion (every training day), cigarette craving (3 times per week), and evaluation of the three interventions (three days per week). Instances of relapse and any sleep or physical problems can also be reported. These data will be stored on local servers at the institute, and no personal information will be collected. Between T2 and T3, biweekly telephone screenings will be conducted to assess abstinence or relapse, as well as the amount of cigarette consumption. See study schedule, Fig. 2.

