### Sample size

The sample size was calculated via the software package G*Power (version 3.1.9.4 [51]) on the basis of the number of days of abstinence at posttreatment (day 42). With a sample size of 128 participants (32 participants per group), we achieve a power of 80%, assuming a minimum effect size of f = 0.25 in an ANOVA at a 5% alpha level. This ensures an optimal balance of sample size, information gain, and resource allocation [52]. To account for potential dropouts, three participants per group will be added, resulting in a total population of 140 participants.

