### Baseline Assessment (T1)

After recruitment, screening, and assessment of the inclusion and exclusion criteria, all participants are assigned to one of the four intervention groups and undergo a baseline assessment (T1). This includes obtaining fully informed written consent and conducting a diagnostic interview to validate TUD and any comorbid mental disorders [48]. Additionally, participants must undergo a physical examination to determine their suitability for participating in HIIT and to establish their individual maximum heart rate. The participants are then asked to complete various questionnaires, psychological assessments, and neurophysiological assessments, with an overview of the utilized questionnaires provided in Table 1.

Subsequently, participants undergo approximately one hour of fMRI, which includes two experiments (the N-back task and the stop-signal task (SST)), resting-state fMRI, and anatomical measurements. In addition, the participants undergo polysomnography.

SST: The SST is conducted during fMRI assessment to evaluate response inhibition [58]. The participants are instructed to respond to arrows, indicating left or right directions, by pressing the corresponding key on a remote control held in their hand with the respective thumb. In approximately 20% of the trials, a stop signal represented by an upwards-pointing arrow appears shortly after the presentation of a left or right arrow. The participants are required to withhold their response when the stop signal appears [59]. The task lasts for 13 min and comprises 320 go trials and 80 stop trials, with the aim of achieving an average of 50% stop successes and 50% stop errors. To maintain this balance, the time between the presentation of the go signal (left or right arrow) and the appearance of the stop signal (upwards-pointing arrow) is adjusted dynamically during the experiment. This adjustment, known as the stop signal delay time (SSD), is increased by 50 ms following a successfully inhibited response and decreased by 50 ms after failure. A longer SSD indicates better inhibitory performance. The reaction time and stop-signal reaction time are subsequently computed to estimate response latency in inhibition [60]. Test-retest reliabilities of neural activity during response inhibition were shown to be good [61].

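### A single, published block size of 8 in an open-arm trial makes up to about one allocation in seven deducible by anyone who sees earlier assignments

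*Protocol article*

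**What the plan says.** Under Study population and design, the article gives the allocation rule: "Stratified (men/women) block randomization with permuted blocks of size 8 will be used". The same section sets the numbers: "A total of 128 participants will be randomized into four groups (4 × 32 smokers". It then defines the two arms with chess training: "Groups 1 and 2 will receive CRT + HIIT either in the evening or morning, respectively". The other two arms leave the chess training out: "Group 3 and Group 4 will receive only HIIT in the evening or morning, respectively". The Sample size section adds a dropout allowance: "three participants per group will be added, resulting in a total population of 140 participants".

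Under Setting, the sport medical examination is placed at an outpatient cardiology clinic, while "the other assessments will be conducted at the Central Institute of Mental Health, Mannheim, Germany".

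Under Baseline Assessment (T1), after recruitment, screening and a check of the eligibility criteria, "all participants are assigned to one of the four intervention groups and undergo a baseline assessment (T1"). The next sentence says of that visit: "This includes obtaining fully informed written consent and conducting a diagnostic interview". The physical examination for fitness to train is listed there too.

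The article does not say who holds the list, how the next assignment is concealed, or whether those who recruit can see earlier assignments.

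**The concern.** Neither the chess training nor the time of day can be hidden from participants, and staff who handle the training data can recognise the arm. Under a fixed block size, earlier allocations carry information about the next one, and the last place in every block is fully determined. Concealing the list does not remove this, because the prediction comes from allocations already made and not from the list.

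If a recruiter can predict the next arm, the timing or the fact of a candidate's entry could depend on it. The text leaves some room for this. Candidates are first screened by telephone. A sleep-disorder diagnosis is worded as something that can, not must, lead to exclusion. Assignment is named before a T1 visit that includes consent and the diagnostic interview. Motivation to quit and daily routine plausibly relate to abstinence, so selection on them could distort the comparisons between arms and would be hard to correct in analysis.

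**Working it through.** **The plan's own figure.** The article states no predictability figure. Its one computed design figure is 128 participants for 80% power at f = 0.25 and 5% alpha. With noncentrality 128 × 0.25² = 8, four cells and a one-degree-of-freedom effect, power is 0.801, so 128 reproduces. It is not affected by this point.

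**Inputs.** From Study population and design: block size 8, four equal arms, strata by sex, 128 randomised. From Sample size: 140 with the dropout allowance. Derived: 8/4 = 2 places per arm per block; 128/8 = 16 blocks; 140/8 = 17.5 blocks. Assumption: the observer knows the block size, every earlier assignment in the stratum, and where blocks begin.

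**Exact arm known with certainty.** The 8th place is always known. The 7th is known only if the last two places belong to the same arm, which has probability 1/7. No earlier place can be certain, since three or more places remain and an arm has only two.

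(1 + 1/7)/8 = 14.3%; 128 × 0.143 = 18.3; 140 × 0.143 = 20.0.

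**CRT or no CRT known with certainty.** A block holds four of each. With r places left, all are of one kind with probability 2·C(4,r)/C(8,r):

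- r = 4 (5th place): 2/70 = 0.029
- r = 3 (6th place): 8/56 = 0.143
- r = 2 (7th place): 12/28 = 0.429
- r = 1 (8th place): 8/8 = 1

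The sum is 1.6 places per block, and 1.6/8 = 20.0%: about 26 of 128, or 28 of 140. Morning versus evening has the same structure and the same result.

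**Best guess of the arm.** The observer always names an arm with most places left. Enumeration of all 2,520 orderings gives:

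| Place in block | 1 | 2 | 3 | 4 | 5 | 6 | 7 | 8 |
|---|---|---|---|---|---|---|---|---|
| Correct | 25.0% | 28.6% | 33.3% | 40.0% | 44.3% | 47.6% | 57.1% | 100% |

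The expected number correct is 3.76 of 8, or 47.0%: about 60 of 128, against 32 by chance. For CRT yes or no, the expected number correct per block is 4 + 256/140 − 0.5 = 5.33, and 5.33/8 = 66.6% against 50% by chance.

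**Alternatives.** For the varying schemes, the guess rates come from simulation with 64 per sex stratum (an equal split is assumed) and sizes drawn at random and undisclosed. The observer names the arm with fewest allocations so far.

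| Scheme | Arm certain | Arm guessed correctly |
|---|---|---|
| Fixed 4, known | 25.0% | 52.1% |
| Fixed 8, known (the plan) | 14.3% | 47.0% |
| Varying 4, 8, 12 | about 3.5% | 45.9% |
| Varying 8, 12, 16 | about 2% | 43.0% |

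Varying the sizes removes most of the certain allocations but lowers the overall guess rate only modestly. Including blocks of 4 gives up part of the gain.

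**The case against.** The strongest objection is that the premise is not in the document. Nothing states that recruiters see earlier assignments. The components that separate the arms are delivered by app or at home, all arms share the cessation programme, and a telephone screener need not know anyone's arm. Separation of roles may well be set out in the full protocol, and its absence from an article is no fault. This stands, and it makes the point conditional. It does not remove it, because the fixed size is a stated rule and its publication helps anyone who does see the assignments.

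A second objection is that the percentages assume a perfect tally by sex, known block starts and assignment one person at a time. The cessation programme runs in groups. If several people are assigned together, there is less scope to delay or redirect one of them. This also stands: the figures are a ceiling. The first two places in a block are at or near chance.

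A reader might infer that staff can foresee allocations generally, or that the primary comparisons will be biased. The documents support neither. Certainty reaches about one allocation in seven, and predictability measures opportunity, not bias. A reader might also blame the stratification by sex, but it adds no predictability and only means that two tallies are kept.

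Finally, a block of twice the number of arms is a common choice and contradicts nothing else in the article. That is fair. This is an avoidable weakness in the design, not an error or inconsistency.

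**Conclusion.** The concern holds in conditional form. By fixing and publishing a block size of 8 in an open-arm, essentially single-centre trial, the plan allows an observer of earlier assignments to deduce up to about 14% of arms and about 20% of CRT-or-not assignments, and to guess the arm at 47% against 25%. This rests on access to the running assignments by sex and knowledge of block starts, neither of which the article confirms. It could permit selection bias; it does not demonstrate any, and no size of bias in abstinence can be derived from the document.

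The T1 wording adds to the point. Assignment is named before a visit that includes consent and the diagnostic interview. The same sentence puts a check of the eligibility criteria beforehand, so the order may be only loosely worded, but as written the arm could be known before enrolment is complete.

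**What to change.** - Replace the fixed size with randomly varying block sizes in multiples of four within each sex stratum, preferably 8, 12 and 16 and without 4. Keep the sizes in a document that recruiting staff cannot see.
- Have the list generated by someone outside enrolment, and keep recruiters from the running assignments by sex. Because varying sizes alone lowers guessing only from 47% to about 43%, this step matters at least as much.
- State in the T1 section that assignment is made only after consent and eligibility are complete.
- If recruitment has begun, apply this to the remaining blocks.

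The cost is a change to the list-generating program and a procedural step, with no extra participants. Running balance becomes slightly looser: within a stratum, the largest possible difference between two arms partway through a block rises from 2 (8/4) to 4 (16/4), which is small at 128 to 140 participants.

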**Fig. 2 Fig2:**
[figure not shown]
Study schedule and measurement time points. CRT: cognitive remediation treatment; fMRI: functional magnetic resonance imaging; HIIT: high-intensity interval training; SCP: standard smoking cessation program

### Sample size

The sample size was calculated via the software package G*Power (version 3.1.9.4 [51]) on the basis of the number of days of abstinence at posttreatment (day 42). With a sample size of 128 participants (32 participants per group), we achieve a power of 80%, assuming a minimum effect size of f = 0.25 in an ANOVA at a 5% alpha level. This ensures an optimal balance of sample size, information gain, and resource allocation [52]. To account for potential dropouts, three participants per group will be added, resulting in a total population of 140 participants.

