**Fig. 1 Fig1:**
[figure not shown]
Schematic display of the study rational. The study aims to improve treatment outcomes in participants with TUD by enhancing cognitive control and sleep quality, thereby counteracting the hypothesised imbalance in regulatory control towards the habit system

We hypothesise that a combination of CRT and HIIT in the evening will enhance treatment outcomes to a greater extent than sleep enhancement via HIIT alone or a combination of CRT and HIIT in the morning. This will be reflected in more abstinence days or fewer cigarettes smoked following relapse. Furthermore, we hypothesise that improved cognitive control is mirrored in improved behavioral results in neuropsychological tasks and changes in neural activity, e.g., during tasks assessing response inhibition or working memory. We predict that these changes are associated with both craving and treatment outcomes.

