### Hypotheses

Primary hypotheses and treatment outcomes:

A combination of CRT + sleep enhancement (i.e., CRT + HIIT early evening) as a six-week add-on therapy enhances treatment outcomes (i.e., relapse and craving) in smokers in comparison to CRT (i.e., CRT + HIIT morning) or sleep enhancement (i.e., no CRT + HIIT early evening) alone.The changes in neural measures of response inhibition, working memory and network connectivity in the salience network following the six-week treatment from baseline will be associated with self-reported craving and perceived stress, as well as treatment outcomes.

2.Secondary hypotheses and mechanisms:

Improvement in cognitive function in smokers.

c.CRT, as a six-week add-on training, improves cognitive function in smokers (i.e., CRT + HIIT in the morning versus HIIT in the morning).

d.Sleep enhancement (induced by HIIT in the evening) as a six-week add-on training improves cognitive function in smokers (i.e., HIIT in the evening versus HIIT in the morning).e.The combined effect of sleep enhancement and CRT (i.e., the interaction effect of CRT × sleep enhancement) increases cognitive function even further.

Improvement in neuronal abnormalities.

f.CRT alleviates neural dysfunction during cognitive performance in smokers (i.e., CRT + HIIT in the morning versus HIIT in the morning).g.Sleep enhancement as a six-week add-on therapy ameliorates neural dysfunction during cognitive performance in smokers (i.e., HIIT in the evening versus HIIT in the morning), as reflected by neural measures of response inhibition, working memory and connectivity strength within the salience network.h.The combined effect of both training methods is even greater (i.e., the effect of CRT + HIIT in the evening versus HIIT in the morning).i.CRT as well as sleep enhancement (i.e., HIIT in the early evening) as a six-week add-on therapy reduces connectivity strength in the salience network.

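### The stated 80% power fits a one-degree-of-freedom contrast on all 128 participants; each 32-versus-32 comparison in the primary hypothesis has about 50% at d = 0.5

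*Protocol article*

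**What the plan says.** The Sample size section bases the calculation on days of abstinence at day 42, run in G*Power. With 128 participants in four groups of 32, it states that "we achieve a power of 80%, assuming a minimum effect size of f = 0.25 in an ANOVA at a 5% alpha level". Three per group are added for dropout, giving 140. The section does not say which effect is tested or give the numerator degrees of freedom.

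The first primary hypothesis (Hypotheses section) is that CRT plus early-evening HIIT improves treatment outcomes "in comparison to CRT (i.e., CRT + HIIT morning) or sleep enhancement (i.e., no CRT + HIIT early evening) alone". Aims and objectives puts it directionally: the evening combination should improve outcomes "to a greater extent than sleep enhancement via HIIT alone or a combination of CRT and HIIT in the morning". Under Study population and design, each of these regimens is one randomised group of 32: Group 1 is the evening combination, Group 2 the morning combination and Group 3 evening HIIT alone.

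**The concern.** The primary question is Group 1 against Group 2 and Group 1 against Group 3, each 32 versus 32. The Sample size section attaches 80% power to an unspecified ANOVA on all 128 participants. A contrast that splits 128 into two halves of 64 has far more information than a comparison of two arms of 32 at the same standardised difference, so the 80% cannot simply be carried over.

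Readers will take the 80% to apply to the primary hypothesis. If the comparisons are then non-significant, the result could be read as evidence that the evening combination adds nothing, when the trial had roughly an even chance of detecting the stated effect in either comparison.

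**Working it through.** **Inputs.** From the Sample size section: N = 128, four groups of 32, f = 0.25, alpha 5%, power 80%, one post-treatment value. From Hypotheses and Aims: the comparisons Group 1 v 2 and Group 1 v 3. Assumptions: two-sided tests (no one-sided test is stated) and equal variances.

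**1. Reproducing the 80%.** For a fixed-effects ANOVA the noncentrality is λ = f²N = 0.25² × 128 = 8, with 128 − 4 = 124 error df. Power is the probability that a noncentral F exceeds the 5% critical value.

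| Numerator df | Critical F | Power at N = 128 | N needed for 80% |
|---|---|---|---|
| 1 | 3.92 | 80.1% | 128 |
| 2 | 3.07 | 70.6% | – |
| 3 (four-group test) | 2.68 | 63.9% | 179, so 180 balanced |

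Only one numerator df returns the printed power, and 128 is then exactly the smallest N that reaches it.

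**2. Power for one primary comparison.** For two equal groups d = 2f = 0.5. With n = 32 per arm, the noncentrality is d√(n/2) = 0.5 × √16 = 2.0. The two-sided critical t on 62 df is 1.999, and power is 50.4%. With the pooled error of all four arms (124 df) it is 51.0%. For comparison, 64 versus 64 gives 0.5 × √32 = 2.83 and 80.1%. If all 35 per arm are analysed, power is 54.1%.

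**3. Power for both comparisons.** The two tests share Group 1, so they are correlated. Simulation at d = 0.5 for each gives 34% with both significant (34–35% with pooled error).

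**4. Other ways of reading f = 0.25.** If it is an effect across four groups, d depends on the pattern of means. Write σ_m for the standard deviation of the four group means, in units of the within-group SD, so that f = σ_m.

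- Only the evening combination differs, means (d, 0, 0, 0): σ_m = d√3/4, so d = 0.25 × 4/√3 = 0.577.
- Two equal additive effects totalling f = 0.25: σ_m = d/√2, so d = 0.25 × √2 = 0.354.
- Largest d common to both comparisons: means (d, 0, 0, d/3) give σ_m = d/√6, so d = 0.25 × √6 = 0.612.

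| d | Each comparison | Both | At least one, unadjusted |
|---|---|---|---|
| 0.354 | 29% | 15% | 42–43% |
| 0.5 | 50–51% | 34% | 67% |
| 0.577 | 62–63% | 47% | 78% |
| 0.612 | 67–68% | 52–53% | 82–83% |

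(Ranges: two-arm and pooled error.) One comparison alone can reach about 80%, if Group 1 and one comparator are the extremes and the other two groups lie midway: d = 0.25 × √8 = 0.707. The other comparison then has d = 0.354 and 29% power, and both are significant in 27% of trials.

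**5. Detectable difference.** For 32 versus 32, 80% power needs d = 0.71 (f = 0.71/2 ≈ 0.36). At d = 0.5, 80% on each comparison would need 64 per group.

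**The case against.** The strongest reply is that no number in the Sample size section is wrong: 128, f = 0.25, 5% and 80% agree for a one-df test. The section never says that the 80% applies to pairwise tests, and the Statistical analyses section plans repeated-measures multivariate analyses and regression, not two t tests. That much stands. The one-df basis is also inferred, and main effects and the interaction are not its only candidates. A planned contrast of the evening combination (32) against the other three arms together (96), at d = 0.577, also has 80.1% power.

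That contrast includes morning HIIT alone, which the primary hypothesis does not name. A contrast of the combination against the average of its two named comparators (32 versus 64) has 63% power at d = 0.5 and 75% at d = 0.577. The CRT-by-sleep interaction is listed among the secondary hypotheses, on cognitive function. Repeated measures cannot be credited, because the calculation uses a single day-42 value and the article gives no within-person correlation.

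A second reply is that the comparators are joined by *or*, so success on either might suffice. Saying that one treatment does better than A or B most naturally means better than both. Under the either reading, unadjusted power is 67% at d = 0.5 and passes 80% only in favourable patterns such as d = 0.612. With each test at 2.5% to control the error rate, that case falls to about 73%. One-sided 5% tests would give 63% per comparison at d = 0.5.

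The exact pairwise figure does depend on how f is translated to d, so it should be reported with its assumption.

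**Conclusion.** The concern holds: as a power statement for the primary hypothesis, the 80% is wrong as written. It belongs to a one-df contrast using all 128 participants. The four-group test has 64%. Each primary comparison has about 50% power at d = 0.5 and both together about 34%. Where f = 0.25 is spread over four groups with an equal difference from both comparators, the figures run from 29% to 68% each and from 15% to 53% jointly. The dropout allowance does not close the gap.

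These figures rest on two-sided 5% tests, equal variances, a single post-treatment outcome and, for the joint figure, the reading that the combination must beat both comparators. The one-df basis is inferred from the arithmetic, but the pairwise power does not depend on what was entered in G*Power.

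**What to change.** Name in the Sample size section the effect and numerator df to which the 80% refers, and report the power of the primary comparisons beside it. Suggested text, with the first sentence to be adapted if another one-df contrast was entered:

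> With 128 participants, a one-degree-of-freedom factorial contrast (CRT versus no CRT, or evening versus morning; 64 versus 64) has 80% power at f = 0.25 and two-sided 5% alpha. For the primary pairwise comparisons (32 versus 32), power at d = 0.5 is about 50% each, and the difference detectable with 80% power is d = 0.71.

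State whether the evening combination must beat both comparators. If so, add the joint power, about 34% at d = 0.5. Do not describe the trial as 80% powered for the primary hypothesis.

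The cost is wording only: no extra participants and no change in conduct. The stated power becomes less favourable.
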